#### **Quantitative assessment of sleep**

- Polysomnography, will be performed on day 3 after randomization to ensure the clearance of drugs that could alter the architecture of sleep. A portable device will be used (Nox A1 System®, Reykjavík, Iceland). Recording will last 9 h, starting at 10:00 p.m. and ending at 07:00 a.m. PSG will include electroencephalography (EEG) with electrodes placed at O1/A2 and C4/A1 according to the international 10-20 system, electromyography (electrodes will be located on the levator menti muscle), electrooculography (left superior canthus, right inferior canthus), electrocardiography, and pulse oximetry will be recorded. PSG will report sleep efficiency, total sleep time, latency, proportion of different stages of sleep, presence of sleep fragmentation, presence of micro-arousals, presence of apneas, registration of eye and limb movements. Sleep recordings will be visually scored by a sleep

specialist physician blinded to the group assignment using international criteria (66). Although PSG is the gold standard for evaluating sleep, because it is a complex and expensive exam, it will only be done once on day 3.

- Actigraphy, is the continuous measurement of an individual's movement using a wristwatch-like device (ACT-Trust® AT0503, Sao Paulo, Brazil). It is an objective method of quantifying sleep and circadian rhythm (67-69). All patients will have an actigraph placed on their non-dominant wrist immediately after randomization and until 1 week after ICU discharge. The main advantages of actigraphy compared to PSG are that it can be monitored continuously through several days, and the data registered is not intrinsically altered by medication (in contrast to EEG). Markers of sleep and circadian function derived from actigraphy include: circadian timing of each 24 hours of greatest activity (within each 24 hour period), sleep duration, sleep fragmentation, and regularity of circadian rhythmicity. All actigraphy data will be analyzed by a sleep physician blinded to the group assignment, using MATLAB (Mathworks, Natick, Massachusetts, USA).

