Major factors for sleep deprivation in critically ill patients are the type and severity of underlying illness, the pathophysiology of the acute illness, pain (from procedures or the underlying condition), and stress/anxiety (6). Mechanical ventilation (MV) may also contribute to sleep disruption in critically ill patients. Sleep in mechanically ventilated patients is highly fragmented (6-12). However, studies that have examined PSG in these patients have observed the same patterns of sleep architecture as in patients without MV (9-12). Similarly, several commonly used ICU medications, including vasopressors, antibiotics, sedatives, opioids, and analgesics, may have profound effects on sleep quantity and quality (6,9-12). Although these factors related to patients' condition play a large role in sleep disruption, they are difficult to modify. However, factors associated to the ICU environment have also been reported to have a major role in sleep disturbance (e.g, lighting, noise, patient care activities), but they can be modified by changes in ICU design and culture (20).

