### **Primary outcome**

- 1) Sleep quantity (time in slow wave sleep-N3 and time in Rapid eye movement-REM) assessed by PSG at day 3

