#### **Inclusion criteria:**

- Patient under invasive mechanical ventilation for at least 72 hours
- Patient without sedation or with superficial sedation level (SAS 3-4 by Sedation-Agitation Scale [65]), during most of the daytime within the 24 previous hours

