#### **d. Randomization**

Patients who meet criteria and who are hospitalized in a modified ICU room will be invited to participate in the study. However, if a patient meets criteria, but is placed in another room, he/she can be transferred to any of the modified rooms if any of them is free. Once the Informed Consent signature is obtained, patients will be randomized to receive a multifaceted intervention of environmental control in the ICU (dynamic light therapy, auditory masking, and rationalization of ICU nocturnal patient care activities) (intervention group) or standard care (control group). The randomization sequence will be generated by a computer program with an allocation 1:1. Due to the type of intervention under study the patient and the research team can't be blinded to the group assignment. Nonetheless, statisticians and the researchers responsible for analysis of PSG and actigraphy, as well as those performing long-term outcome assessments will be blinded to the group allocation.

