#### ▪ **Common procedures for both groups**

To avoid bias, in both groups the protocol of analgesia and sedation of the unit will be used if the patient requires it. Level of sedation will be monitored as part of daily care by nurses in all patients every four hours using the Sedation-Agitation Scale. In our unit benzodiazepines are not used except when the patient uses them chronically or to avoid drug and alcohol withdrawal syndrome. In case patients admitted to the study present delirium, they will be treated according to the institutional protocol for management of delirium, independent of the study group. In our unit, melatonin and other sleep inducers are not used routinely.

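### Day-3 timing cannot ensure that sleep-altering drugs have cleared, because sedation is allowed at entry and afterwards; reword the claim, adjust for baseline sedation and report drug exposure by arm

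*Protocol*

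**What the plan says.** The primary outcome is "Sleep quantity (time in slow wave sleep-N3 and time in Rapid eye movement-REM) assessed by PSG at day 3", from one overnight recording (10 p.m. to 7 a.m.). The section on quantitative assessment of sleep explains the timing: PSG "will be performed on day 3 after randomization to ensure the clearance of drugs that could alter the architecture of sleep".

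Four other places bear on that statement.

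- **Inclusion criteria (III.c).** Eligible is a "Patient without sedation or with superficial sedation level (SAS 3-4 by Sedation-Agitation Scale"), judged "during most of the daytime within the 24 previous hours".
- **Common procedures for both groups (III.e).** After randomisation, "in both groups the protocol of analgesia and sedation of the unit will be used if the patient requires it". Benzodiazepines are restricted, with two exceptions, and sleep inducers are not routine. No limit is stated for opioids or other sedatives. The Sedation-Agitation Scale (SAS) is recorded every four hours.
- **Sleep in critical illness (I.2).** The background states that "several commonly used ICU medications, including vasopressors, antibiotics, sedatives, opioids, and analgesics, may have profound effects on sleep quantity and quality".
- **Randomization (III.d) and statistical analysis (III.g).** "The randomization sequence will be generated by a computer program with an allocation 1:1"; no stratification factor is named. Continuous outcomes are compared by t-test or Mann-Whitney test, with no covariate. Daily drug doses are collected (III.f), but no use of them in the primary comparison is described.

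**The concern.** The protocol presents the day-3 timing as a safeguard for its primary endpoint, and its own rules do not provide that safeguard. This matters for two reasons. The endpoint rests on a single EEG night, so no repeat recording can reveal or average out a drug effect. The protocol also says, when it contrasts actigraphy with EEG, that medication alters EEG data.

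Drug exposure that differs between patients on the recording night adds to the spread of N3 and REM time, and with 28 per arm it may fall unevenly by chance. Exposure could also come to differ between arms after randomisation. Care is open-label, and only in the intervention arm are medications reviewed and retimed and bedside nurses coached. A reader who trusts the clearance statement would not look for such a difference.

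**Working it through.** **Step 1: the texts side by side.** Clearance by day 3 would require that the relevant drugs are stopped at or soon after randomisation, or that PSG is done only in drug-free patients.

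- At entry, light sedation is allowed. It is judged over most of the daytime, whereas PSG is a night recording.
- After entry, sedation and analgesia are given as required, with no exception for day 3.
- PSG is not made conditional on drug status anywhere.

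Neither requirement is met, so the statement does not follow from the design. The benzodiazepine restriction narrows the gap but does not close it.

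**Step 2: inputs from section III.g.** Control N3 mean 7 min, SD 9 min, target improvement 50% = 3.5 min, total 56 = 28 per arm. The protocol gives no figure for the clearance claim itself. With these inputs, the standard error of the arm difference is 9 × √(2/28) = 2.4 min. Two-sided power at 5% is Φ(3.5/2.405 − 1.96) = Φ(−0.505) = 31%. The stated 80% would need 2 × 81 × (1.96 + 0.84)² / 3.5², or about 104 per arm. That shortfall is a separate issue; 31% is used here only as the base for step 5.

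**Step 3: chance imbalance (sedation rate assumed).** Take two independent binomial counts with n = 28. A difference of at least 20 points means at least 6 patients (6/28 = 21 points).

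| Assumed share sedated | P(difference ≥ 20 points) |
|---|---|
| 20% | 6% |
| 30% | 11% |
| 50% | 14% |

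**Step 4: size of the shift (sedation effect assumed).** Shift = imbalance × effect of sedation on N3.

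| Assumed effect on N3 | Shift at 20 points | Share of 3.5 min target |
|---|---|---|
| 3.5 min | 0.7 min | 20% |
| 7 min | 1.4 min | 40% |
| 9 min (one SD) | 1.8 min | about 50% |

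The last row is extreme, since 9 min exceeds the expected mean of 7 min. Even there, the shift is below one standard error. A shift as large as the target would need 3.5/9 = 39 points, or 11 patients. Its probability is 0.2% at 30% sedated and 0.5% at 50%.

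**Step 5: what adjustment could recover (R² assumed).** If a baseline factor explains a share R² of the variance, the standard error shrinks by √(1 − R²).

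| R² | Standard error | Power at 28 per arm |
|---|---|---|
| 0 | 2.41 min | 31% |
| 10% | 2.28 min | 34% |
| 20% | 2.15 min | 37% |
| 30% | 2.01 min | 41% |

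A two-level factor with prevalence p and effect d explains p(1 − p)d²/81. For p of 30-50%, this is 3-4% at d = 3.5, 13-15% at d = 7 and 21-25% at d = 9. The 30% row is therefore optimistic.

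**The case against.** The strongest reply is that this is a matter of wording. Allocation is randomised 1:1, so sedation is balanced in expectation. Its variation is already part of the 9 min SD, and the 5% error rate of the test allows for it. The protocol also takes other measures: deeper sedation is screened out for most of the preceding daytime, benzodiazepines are restricted, one sedation protocol covers both arms, and SAS is recorded every four hours. An unadjusted two-group test is valid, and covariates are often left to a statistical analysis plan, which is not at hand.

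Most of this stands. A reader might infer that the primary comparison is biased, or that chance imbalance could readily produce or hide an effect of the target size. The documents support neither: imbalance at randomisation is chance, and a shift of 3.5 min is very improbable even with an extreme assumed effect.

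It is also fair to say that sedation at entry is only a proxy for sedation on day 3, since patients may be weaned in between. The eligibility check does not require a record of whether a patient was unsedated or lightly sedated, so a factor would need its own definition.

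The reply does not rescue the clearance statement, which remains unsupported by the entry and care rules. Nor does it explain why the drug data already collected have no stated role.

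**Conclusion.** The concern holds in a limited form. The protocol claims a property for its primary endpoint that its design does not have, and the passages must be reconciled. The consequence is lost precision and harder interpretation. Validity of the randomised comparison is not affected.

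Illustratively, a 20-point imbalance moves the N3 difference by 0.7-1.8 min, 20-50% of the target. Adjustment would raise power from 31% to 34% if baseline sedation explains 10% of the variance, and to 41% if it explains 30%. The sedation rate, its effect on N3 and R² are all assumptions, because the documents give none of them. If most patients are free of these drugs by day 3, the gain is smaller still.

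Drug exposure after randomisation is a different matter. It could differ between arms because care is open-label and medications are retimed in one arm. The documents do not show that it will, which is a reason to report it rather than to presume bias.

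**What to change.** 1. **Reword the timing rationale.** Remove the clearance claim, or restate it so that it agrees with the inclusion criteria and the common procedures. No change to sedation practice is proposed here.
2. **Define one baseline factor:** sedated or not sedated in the 24 h before randomisation, with an explicit rule based on the eligibility check, SAS and dose records. Include it as a pre-specified covariate in the primary N3 and REM comparisons. If a rank test is kept, use its stratified version. If the randomisation list is not yet fixed, use the same factor as a stratum.
3. **Tabulate sedative and opioid exposure in the 24 h before PSG by arm,** from the daily dose data.
4. **Do not adjust the primary analysis for sedation given after randomisation.** The intervention may influence it, so conditioning on it could distort the comparison.

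The cost is a written definition, a recorded entry status, one covariate (two lists if stratified) and one table. The limit is that entry status captures day-3 exposure only in part, so the precision gain may be small.

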### ***Qualitative assessment of sleep***

- Richards-Campbell Sleep Questionnaire (RCSQ)(70): this is a five-item, visual analogue scale designed to assess the perception of sleep in patients who are critically ill. The scale evaluates perceptions of depth of sleep, sleep onset latency, number of awakenings, time spent awake and overall sleep quality. Patients will complete the questionnaire as they reflect on their previously night, starting from the second day of enrollment until ICU discharge.
- Pittsburgh Sleep Quality Index (PSQI)(71): the PSQI is a self-rated questionnaire, assessing sleep quality over a 1-month time interval. Nineteen individual items generate a seven-component score: subjective sleep quality, sleep latency, sleep duration, habitual sleep efficiency, sleep disturbances, use of sleeping medications and daytime dysfunction. The sum of scores for these seven components yields one global score. Patients will completed the questionnaire at 6 months post ICU discharge.

**Assessment of circadian rhythm :** Melatonin and cortisol plasmatic levels will be assessed at the day 1 and 3 after randomization. Four samples will be taken each day. Plasmatic melatonin levels will be measured with Melatonin ELISA Kit, according to the manufacturer's instructions (ABCAM, USA). Plasmatic cortisol levels will be analyzed in the laboratory of the University Hospital of the Pontificia Universidad Católica de Chile.

**Light and noise measurements:** A sonometer (Cirrus CR:172B, Cirrus Research, UK) and a luxometer will be placed near the patient's head. Ambient sound will be measured continuously and illuminance will be measured every 30 minutes until ICU discharge. These data will be registered and analyzed later by light and sound experts.

**ICU Delirium:** The presence of delirium will be evaluated once daily using the Confusion Assessment Method for the ICU (CAM-ICU)(72) starting immediately after randomization and until ICU discharge. Prevalence of delirium will be defined as the presence of delirium (positive CAM-ICU screening) on at least 1 day during ICU stay. Duration of delirium will be defined as total days of delirium during ICU stay.

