### **Secondary outcomes**

- 1) Total time of sleep assessed by actigraphy
- 2) Sleep quality assessed by questionnaires (RCSQ and PSQI)
- 2) Circadian timing: Oscillation of plasma concentration of Melatonin and Cortisol
- 3) ICU delirium (prevalence and duration of delirium in ICU) by Confusion Assessment Method for the ICU (CAM-ICU)
- 4) Neuropsychological impairment (depressive symptoms and cognitive impairment) at 6 months post ICU discharge by cognitive testing and instrument screens of depression

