#### **Exclusion criteria:**

- Patient who required mechanical ventilation in another episode of hospitalization in the 2 months before screening
- Patients with primary neurological or neurosurgical disease

- Presence of mental or intellectual disability prior to hospitalization or communication/language barriers
- Pre-existing comorbidity with a life expectancy not exceeding 6 months (eg, metastatic cancer)
- Readmission to the ICU (patients can only be included if they are on their first ICU admission of the present hospitalization)
- No fixed address for follow-up
- Patients with moderate to severe visual or hearing impairment
- Patients with known sleep disturbance before hospital admission
- Early limitation of therapeutic effort

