#### **f. Study variables**

- 1. Baseline parameters to be collected:** At the time of enrolment, information collected on each patient will include the following: patient demographics, dates of hospital and ICU admission, illness severity according to the Acute Physiology (APACHE II), Chronic Health Evaluation II and Sequential Organ Failure Assessment Score (SOFA), comorbidities according to the Charlson Comorbidity Index, admission diagnoses, and pre-existing neuropsychological impairment.
- 2. Repeated assessments to be performed during the study protocol:** During the course of each patient's stay in the ICU data will be collected on: Sequential Organ Failure Assessment Score (SOFA), Partial pressure of oxygen (PaO2)/Fraction of inspired oxygen (FiO2), daily arterial pressure and minimum glycemia value obtained, daily doses of medications. Use of hemodialysis and vasopressors, mechanical ventilation duration and ICU/Hospital length of stay data will be collected also. All patients will undergo a standardized follow-up immediately prior to hospital discharge and at 6 months later. At 6 months patients will attend to a follow-up visit, and if they are unable to attend they will be visited at home.

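### Plasma cortisol is used as a circadian marker in all patients with no condition on systemic corticosteroids, so in any patient given them the profile does not measure circadian timing

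*Protocol*

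**What the plan says.** Under Secondary outcomes the protocol lists "Circadian timing: Oscillation of plasma concentration of Melatonin and Cortisol". Specific goal 2 consists of comparing this oscillation between arms. The paragraph on assessment of circadian rhythm (section III.f) fixes the measurement: "Melatonin and cortisol plasmatic levels will be assessed at the day 1 and 3 after randomization", and "Four samples will be taken each day". No condition on treatment received is attached.

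The population is defined by "Patient under invasive mechanical ventilation for at least 72 hours" and by light or no sedation. The exclusion criteria name neither corticosteroids nor melatonin; the nearest item is "Patients with known sleep disturbance before hospital admission". Under Common procedures for both groups the protocol says that "melatonin and other sleep inducers are not used routinely" in this unit and sends delirium treatment to an institutional protocol whose content is not given. Section III.f collects "daily doses of medications" during the ICU stay, with no mention of dose times. Section III.g analyses by intention to treat and gives no separate rule for hormone profiles. Corticosteroids are not mentioned anywhere in the text.

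**The concern.** A plasma cortisol profile is a circadian marker only if the cortisol is the patient's own and its secretion is not suppressed. Hydrocortisone is cortisol, so the measured curve follows the dosing times. Other systemic corticosteroids suppress endogenous secretion and flatten the curve. This is general pharmacology, not a statement in the protocol. With four samples a day and no dose times, a dosing peak cannot be told from an endogenous one.

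The protocol shows this kind of care elsewhere. Under Quantitative assessment of sleep it places polysomnography on day 3 so that drugs affecting sleep architecture can clear, and counts it an advantage of actigraphy that medication does not intrinsically alter the recording. The hormones, which a given hormone affects most directly, have no such safeguard and are sampled from day 1.

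At stake is the reading of goal 2. A null cortisol result could mean that the intervention does not move the rhythm, or that too many profiles contained no rhythm to move. The data as planned could not separate the two.

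**Working it through.** **Text check.** The places where a condition could stand are:

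- Inclusion and exclusion criteria: nothing on corticosteroids, given melatonin or adrenal disease.
- Common procedures: melatonin is described as not routine and is not prohibited; corticosteroids are not mentioned.
- Assessment of circadian rhythm: days, number of samples and laboratory methods only.
- Study variables: daily doses are recorded, so exposure can be identified by day but not related to the time of a sample.
- Statistical analysis: one general intention-to-treat sentence.

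**Size.** The protocol states no figure for this outcome, so there is none to reproduce. The following is an illustration only.

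Inputs: 56 patients (section III.g); two-sided alpha of 5%; an effect on cortisol oscillation that would have 80% power if all 56 profiles were clean (assumption); share f of patients exposed to systemic corticosteroids, equal in both arms (assumption, 10% to 30%, not in the documents).

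With z(0.975) = 1.960 and z(0.80) = 0.842, the standardised effect in 56 clean profiles is 1.960 + 0.842 = 2.802. Power is then Φ(k × 2.802 − 1.960), where:

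- k = 1 − f if exposed profiles are kept, carry no intervention effect and have the same spread as the others;
- k = √(1 − f) if exposed profiles are set aside and the sample shrinks.

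| f | Exposed of 56 | Kept | Set aside |
|---|---|---|---|
| 10% | 56 × 0.10 = 5.6, about 6 | Φ(0.900 × 2.802 − 1.960) = Φ(0.56) = 71% | Φ(0.949 × 2.802 − 1.960) = Φ(0.70) = 76% |
| 20% | 56 × 0.20 = 11.2, about 11 | Φ(0.800 × 2.802 − 1.960) = Φ(0.28) = 61% | Φ(0.894 × 2.802 − 1.960) = Φ(0.55) = 71% |
| 30% | 56 × 0.30 = 16.8, about 17 | Φ(0.700 × 2.802 − 1.960) = Φ(0.00) = 50% | Φ(0.837 × 2.802 − 1.960) = Φ(0.38) = 65% |

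Setting profiles aside recovers part of the loss, not all of it. Two assumptions pull in opposite directions. If drug-driven profiles vary more than endogenous ones, power with them kept is lower than shown. If some exposed profiles retain part of their rhythm, it is higher. The set-aside column assumes that every exposed profile is identified and removed; a restriction by status at randomisation would miss exposure that begins later.

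**The case against.** The strongest reply is that handling of concomitant medication is normally settled in a statistical analysis plan, which may exist, and that the intention-to-treat sentence does not forbid a rule for exposed profiles. Part of this stands: the absence of an analysis rule alone would not be a finding. But the protocol itself defines the outcome as circadian timing, takes it in every patient, and sets no condition under which the marker is valid. What is captured at the bedside is also a protocol matter, and dose times that are not collected prospectively may not be recoverable.

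Four stronger readings are tempting, and the documents do not support them.

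- *That some profiles will show drug.* Long ventilation makes corticosteroid use plausible, but no rate is given. The statement must stay conditional: in any patient given these drugs.
- *That the melatonin outcome is compromised to the same degree.* The protocol says "In our unit, melatonin and other sleep inducers are not used routinely". This is not a prohibition, and the delirium protocol is not shown, so the possibility remains. Nothing suggests that it is common.
- *That unblinded staff would give melatonin mainly to poorly sleeping controls, multiplying that arm's mean level and hiding or reversing an effect.* No input to such a scenario is in the documents. Any multiplier would also apply to an arithmetic mean, while section III.g allows a rank test when data are not normal.
- *That all exposed sample-days should simply be dropped.* Exposure after randomisation may depend on arm. If sleep aids did go to poor sleepers in one arm, removal would take those patients out of that arm only and bias the comparison.

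It is also fair that randomisation balances corticosteroid use already present at entry in expectation. That part therefore dilutes the comparison rather than biasing it.

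**Conclusion.** The point holds for cortisol, conditionally on exposure. The protocol takes plasma cortisol as a circadian marker in all patients and does not address the drugs that replace or suppress it. In an exposed patient the profile does not measure what goal 2 asks. The size cannot be fixed from the documents: the loss from 80% power to about 71% at 10% exposure, or 50% at 30%, rests on the assumed rates, on complete loss of signal in exposed profiles, and on equal exposure and spread. For melatonin only a recording need remains. The sample size rests on N3 sleep time, so the primary polysomnography outcome is not affected. The change is worth making because it is cheap and has to be in place before sampling.

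**What to change.** In the paragraph on assessment of circadian rhythm, state that:

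1. The cortisol oscillation comparison is made in patients not receiving systemic corticosteroids at randomisation. Allocation cannot affect this status, so the restriction does not break the randomised comparison.
2. The all-patients intention-to-treat result is shown alongside.
3. Later corticosteroid exposure and any given melatonin are flagged from the daily medication record already planned, with time of last dose added on days 1 and 3, and exposure is reported by arm.
4. Removal of exposed sample-days is a sensitivity analysis only, because exposure after randomisation may depend on arm.

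The cost is a short addition to the text and one time-of-dose field on two days. The downside is fewer cortisol profiles and a main cortisol conclusion limited to patients without corticosteroids at randomisation. Patient care does not change.

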### ***g. Sample size and statistical analysis***

According to a previous study, which measured sleep with PSG (63), and other studies, which have described sleep architecture in the ICU (3-7), we estimate that the N3 stage time in our study population will be 7 minutes with a SD of 9 minutes. We considered that a 50% improvement in N3 stage time would be both, clinically relevant and realistic. With a power of 80% and with alpha of 5%, we calculated that a sample size of 56 patients is required to demonstrate statistically significant differences.

General statistical analysis will be performed according to intention to treat. Baseline characteristics will be reported using mean values  $\pm$  standard deviation (SD), or median (p25-75) and proportions where

appropriate. The use of parametric vs non-parametric tests will be decided according to data distribution and the fulfillment or not of normality assumptions. Specific statistical analysis for comparisons between groups will be performed by Student's-t test or Mann-Whitney U-test for continuous variables, and by chi-square for proportions. Changes along time will be analyzed by one-way (repeated-measures) analysis of variance (ANOVA) or Friedman test. Interactions between groups and time we will assessed with two-way repeated-measures ANOVA. All statistical calculations will be performed using Stata Statistical Software, Release 15.1 (College Station, TX). A probability value (p-value) of less than 0.05 will be considered as statistically significant.

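### Delirium duration is a raw count of positive days over each patient's own ICU stay, so early death lowers the count and looks like benefit

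*Protocol*

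**What the plan says.** Delirium is a secondary outcome: "ICU delirium (prevalence and duration of delirium in ICU) by Confusion Assessment Method for the ICU (CAM-ICU"). It also has its own goal (Specific goals, goal 3), which is tied to the ICU stay.

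The ICU Delirium paragraph in section III.f sets three things. CAM-ICU is done once daily, "starting immediately after randomization and until ICU discharge". For prevalence: "Prevalence of delirium will be defined as the presence of delirium (positive CAM-ICU screening) on at least 1 day during ICU stay". For duration: "Duration of delirium will be defined as total days of delirium during ICU stay".

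Section III.g compares groups by "Student's-t test or Mann-Whitney U-test for continuous variables, and by chi-square for proportions". It gives no rule for death, no common horizon and no allowance for days at risk. The day-30 limit in Specific goal 1 belongs to the sleep goal, not to delirium.

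On entry status, the inclusion criteria require "Patient under invasive mechanical ventilation for at least 72 hours". Delirium is not an exclusion criterion. The baseline list includes "admission diagnoses, and pre-existing neuropsychological impairment" but no CAM-ICU before randomisation. The common procedures foresee delirium in enrolled patients: "In case patients admitted to the study present delirium, they will be treated according to the institutional protocol for management of delirium".

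**The concern.** A total of positive days is the daily delirium risk multiplied by the number of days on which the patient could be found positive. The second factor is set after randomisation and differs between patients. A patient who dies on day 2 can contribute at most two delirium days and so scores better than a survivor with three. A day on which the patient is too deeply sedated to be assessed also adds nothing. If the arms differ in death or stay, the duration comparison mixes that difference with any effect on delirium. The protocol says in section I.5 that it cannot test mortality or ICU stay with adequate power, so such a difference could go unrecognised.

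Prevalence raises a separate and smaller issue. The first CAM-ICU comes immediately after randomisation. The masking sound runs only at night, and the re-organisation of night care begins the day after inclusion. A patient positive at that first assessment is counted as a case for good, although the intervention has had almost no chance to act.

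**Working it through.** The protocol states no delirium rate, duration, effect or power, so there is no figure to reproduce. From the protocol come the definitions above, 56 patients and 1:1 allocation (28 per arm). All rates below are assumptions.

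**Duration and early death.** Assume a daily delirium risk of 0.40, a mean stay of 8 days, and early deaths spread evenly over days 1-3 (mean 2 days).
- Expected delirium days: 0.40 × 8 = 3.2 if the patient does not die early, and 0.40 × 2 = 0.8 if the patient does.
- 10% early death: 0.9 × 3.2 + 0.1 × 0.8 = 2.96.
- 40% early death: 0.6 × 3.2 + 0.4 × 0.8 = 2.24.
- Simulation with 400,000 patients per scenario gives 2.96 and 2.23, a fall of about 25% with the daily risk unchanged.
- In the same simulation, at-least-one-day prevalence falls from 92% to 82%.

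**The alternative measure on the same patients.** Take days alive and delirium-free to day 14, scoring an early death as zero.
- 10% early death: 0.9 × (14 − 3.2) = 9.72 (simulated 9.73).
- 40% early death: 0.6 × 10.8 = 6.48 (simulated 6.47). This is the right direction.
- If delirium-free days before death are credited instead (0.6 × 2 = 1.2 days per early death), the results are 9.72 + 0.12 = 9.84 and 6.48 + 0.48 = 6.96, with the same direction.
- To day 30, with an early death scored zero: 0.9 × 26.8 = 24.1 and 0.6 × 26.8 = 16.1.

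**Duration and stay.** With 10% early death, halving the mean stay from 8 to 4 days gives 0.9 × 1.6 + 0.1 × 0.8 = 1.52 delirium days, against 2.97 simulated at 8 days. This is a fall of about 49% at the same daily risk.

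**What the test does.** With a daily risk of 30%, mean stays of 11 vs 8 days and 28 per arm, mean delirium days are 0.3 × 11 = 3.3 and 0.3 × 8 = 2.4. Mann-Whitney rejects in about 17% of simulated trials. With equal stays it rejects in 4-5%, and with 11 vs 10 days in 5.3%.

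**Prevalence.** Let p0 be the share positive at the first assessment, and let new-onset risk be 40% vs 20%. Observed prevalence is p0 + (1 − p0) × new-onset risk.
- p0 = 30%: 0.3 + 0.7 × 0.4 = 58% vs 0.3 + 0.7 × 0.2 = 44%, so 20 points become 14.
- p0 = 50%: 70% vs 60%, so 10 points.
- Power at 28 per arm is 37% with p0 = 0 and 15% with p0 = 40%. Restricting the latter case to patients negative at entry gives 24%.

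**The case against.** The objections have force on several points.

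- A reader might infer that the prevalence comparison is biased. The documents do not support that. The protocol names prevalence, not incidence, and applies the term consistently. Randomisation balances entry delirium in expectation. What remains is dilution and chance imbalance with 28 per arm.
- A reader might infer from the 17% rejection rate that the duration test is generally invalid. It is not. That rate needs an assumed three-day difference in mean stay between arms. If the intervention changes neither stay nor death, the test holds its level.
- A reader might infer that the trial is likely to favour an arm with more deaths. Nothing in the protocol predicts excess early deaths from lighting, sound masking and care scheduling, and the 10% to 40% contrast is an illustration. The defect is that the definition scores in the wrong direction if such a difference arises, by chance or otherwise.
- A shorter stay through faster recovery is a real benefit, and fewer days spent delirious is part of it. It is still not evidence of a lower delirium risk. Stay is therefore a matter of interpretation, and early death is the clearly perverse case.
- Unassessable days are limited by design: entry requires no or light sedation. The unit's sedation protocol may still be used afterwards, so such days can occur.
- An SAP, not at hand, may add handling of death, unassessable days or baseline adjustment. The protocol nevertheless fixes the duration definition itself.

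**Conclusion.** The point on duration holds. As written, the measure has no common window and no rule for death or unassessable days, so early death registers as less delirium. In the illustration the size is about 0.7 days, or 25%. It rests on an assumed 40% daily risk, an 8-day mean stay and a 30-point rise in death on days 1-3. With no difference in stay or death, no distortion arises.

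The point on prevalence is secondary and concerns lost sensitivity only: an assumed 20-point effect shrinks to 14 points if 30% are positive at entry and to 10 if 50% are. Power is low at this sample size under either definition.

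Severity is minor to moderate. This is a secondary outcome, and the trial was not sized on it.

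**What to change.** **Duration.** Define the outcome as days alive without delirium or coma in a fixed window from randomisation, for example to day 30, the horizon already in Specific goal 1. Credit zero days after death, and state how delirium-free days before death and unassessable days are scored. Keep total delirium days as a descriptive result. Add date of death to the study variables, since section III.f does not list it.

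**Prevalence.** Do the first scheduled CAM-ICU just before randomisation instead of just after it. The research team is not blinded and CAM-ICU raters are not among the blinded assessors in section III.d, so a reading taken after allocation is a weaker baseline. Exclude this reading from the outcome, and either adjust for it or report new-onset delirium in patients negative at entry. Excluding it alone is not enough: if entry delirium persists equally in both arms, the difference with 30% positive at entry is still 0.7 × (0.4 − 0.2) = 14 points.

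**Cost.** The change is mostly wording, plus one data item and a shift in the timing of one assessment. Daily CAM-ICU and four-hourly sedation scores are already planned. The drawback is that CAM-ICU stops at ICU discharge, so later days are unobserved and must be assumed delirium-free. The new measure therefore also reflects stay: in the 14-day illustration, halving the mean stay raises it from 9.73 to 11.16 days. This assumption should be stated with the result.
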